#### b) Intention to treat (ITT) and according to protocol (ATP) analysis sets

The analysis of primary and secondary endpoints will be considered two ways. Firstly we will adopt an 'intention to treat' approach where the analysis is carried out using all households that are randomized and for which there are some outcome data. At enrolment of the house, a list of children who normally sleep in the house will be made and updated at the beginning of the rainy season to include newborns and record any changes in occupancy. At blood sampling in November, any children absent will be listed with the reason they were missing. The ITT study population for the anaemia endpoints is all children included in the updated list. Analysis will be limited to those who were sampled for Hb and parasitology in November.

Secondly, we will adopt an 'according to protocol' approach where the analysis is carried out using all houses and study subjects in the control group, but excluding all houses from either intervention group (and study children that slept there) that have screening scored as 'badly damaged' in a durability study conducted 6 months post screening installation. The definition of 'badly damaged' screens will be determined separately for homes in the two treatment arms. In full screened houses damage will equate to 5 or more holes in the screening and/or doors not closing tightly. In screened ceiling houses damage will equate to 5 or more holes in the screening and/or where the netting has come away from the battens that secure the screening to the walls.

ITT and ATP analyses will include stratification by year, by rural/urban, and by block, which were stratification factors in the randomization. There will be no adjustment for the number of children in each trial arm even though this was a stratification factor in the randomization. We stratified to ensure similar numbers in each trial arm for Hb sampling, but the number of children in the house is not expected to relate to any of the clinical outcome measures.

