**Figure 1 F1:**
[figure not shown]
A screened entrance to a thatched house in rural Italy in 1900, in an experiment where screening reduced malaria by 96% [20]. This illustrates that even extremely poor housing can be protected from mosquitoes.

The literature review of Lindsay *et *al. provides compelling evidence that house screening has been associated with protection against malaria transmission, infection and morbidity[12]. Furthermore, a pilot study conducted in The Gambia using experimental huts demonstrated that netting ceilings alone can reduce exposure to malaria vectors by 80%[13]. In this situation, most mosquitoes entered the huts through the open eaves and were effectively trapped in the roof space. Further studies in actual village houses are needed to confirm these findings and to assess the acceptability of the intervention to house-holders.

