### Design

In each of 2 intervention years we will erect; full screening on the door(s) and windows and close the eaves with a mixture of sand, rubble and cement (as is normal local practice) in 100 houses and install screened ceilings in a further 100 houses. 50 houses without any screening will serve as a control group. Thus we will enroll a total of 500 houses over the 2 year study. Screening will be installed prior to the rainy season of each year (January to May). All rooms in the house will be screened, not just the target bedroom(s).

Exposure to mosquitoes will be measured by routine surveillance with light traps, fitted near a participant sleeping under an untreated bednet. All children sleeping in eligible houses will sleep under an untreated bednet and their exposure to malaria parasites estimated by (1) haemoglobin density (Hb), (2) percentage of children with anaemia (<8 g/dL), (3) percentage of children with severe anaemia (<5 g/dL), (4) parasite prevalence and (5) high parasite prevalence (> = 5000 parasites/μl), as determined by a cross-sectional survey at the end of the transmission season. At the end of the trial the participants in the control group will be able to choose to have their houses screened, and participants in either of the screening groups will be able to choose to keep that screening, have it removed, or have it changed to the other type of screening. In addition, insecticide-treated nets (ITN) will be provided to all study subjects at the end of the trial.

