### Interventions

#### a) Full Screening arm

Door frames will be made from 50 × 50 mm softwood. The doors themselves will be constructed from 15 × 30 mm softwood, strengthened at the corners. Sheets of white PVC-coated fibreglass netting (Vestergaard Frandsen group, Denmark) will be stretched and stapled over the doors (Fig 2a). All doors will open inwards and will be hung on the inside of any existing doors, unless prevented from doing so by an immovable obstruction. Handles and push bars will be fitted on both sides of the door and a catch fixed on the inside to hold the door tight in the frame when shut. Elastic cord will be attached to the outside of the door to pull the door closed when not in use. Windows will be made in a similar fashion to the doors. If the occupants do not need to open the window the netting will be stapled straight onto the 50 × 50 mm frame. If there is already a window in place then the screened window will be installed to the inside of the existing window, and a sliding plywood panel fitted to enable access to the outer window (Fig 2b). Eaves will be closed with a mixture of sand, rubble and cement (Fig 2c).

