#### c) Control arm

Control houses receive no screening of any type and the eaves remain open.

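### The ATP damage rule for full-screened houses does not name the eaves, so a house whose closed eaves have re-opened can stay in the ATP set

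*Protocol article*

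**What the plan says.** Under Design, the protocol article describes the full-screening arm as "full screening on the door(s) and windows and close the eaves with a mixture of sand, rubble and cement". The Interventions section, part a, repeats the eave work as its own step: "Eaves will be closed with a mixture of sand, rubble and cement". The arm therefore has three parts: screened doors, screened windows and closed eaves. In the control arm, "Control houses receive no screening of any type and the eaves remain open".

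The Background reports, for experimental huts in the pilot study, that "most mosquitoes entered the huts through the open eaves".

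Analysis, section b, defines two analysis sets. ITT comes first and keeps all randomised households with some outcome data. The second is introduced thus: "Secondly, we will adopt an 'according to protocol' approach". It keeps all control houses and removes intervention houses scored as badly damaged six months after installation. The definition is arm-specific:

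- Full screening: "In full screened houses damage will equate to 5 or more holes in the screening and/or doors not closing tightly".
- Ceiling: five or more holes, and/or "where the netting has come away from the battens that secure the screening to the walls".

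**The concern.** Read as written, a full-screened house with sound netting and tight doors passes, even if its eaves have re-opened. Such a house has lost one of its three barriers and, on that route, is back in the control condition. A ceiling house whose netting has pulled away at the wall edge is removed. The two active arms are thus not judged on the same footing: one rule covers the failure of everything the arm installs, and the other leaves a component out.

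Two ATP results would be touched if eaves do fail. The contrast of full screening with control would be diluted. In the comparison of the two interventions, a poorer full-screening mean would lower the ceiling-to-full ratio and make it easier to declare the ceiling as effective. In that kind of comparison, dilution of the reference arm works towards the favourable conclusion, and an ATP set is normally wanted as a guard against this.

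**Working it through.** **1. Components against the damage rules**

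| Arm | Component installed | Named in the ATP damage rule? |
|---|---|---|
| Full screening | Netting on doors and windows | Yes, five or more holes |
| Full screening | Door closure | Yes, doors not tight |
| Full screening | Eaves filled with sand, rubble and cement | No |
| Ceiling | Netting | Yes, five or more holes |
| Ceiling | Attachment to the wall battens | Yes |

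Could holes in the screening be read to include the eaves? The caption of Figure 2 lists closed eaves under the full-screening installation, which gives that reading some support. Against it, the Design section words screening of doors and windows separately from eave closure, and a count of five holes does not suit a gap in a cement fill. The text is at best ambiguous.

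**2. The plan's own figure for the intervention comparison**

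Inputs from Sample Size Rationale, section a: means 7.5 and 5.0, SD of log catch 1.2, one-sided alpha 0.025, power 90%, expected difference zero.

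n per group = 2 × SD² × (1.960 + 1.282)² / [ln(7.5/5.0)]² = 2 × 1.44 × 10.51 / 0.4055², which rounds up to 185. With the margin rounded to 0.41 it is 181, the stated number. The plan's figure reproduces, so its log-scale inputs can be used below.

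**3. Effect of failed eaves (illustrative)**

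Assumptions, none of which the document supplies:

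- A share f of the full-screened houses kept in ATP have failed eaves.
- Their catch either returns fully to the control value of 15 (worst case) or goes half-way on the log scale.
- The SD stays at 1.2.
- There are 180 houses per arm (200 less 10%), so SE = 1.2 × √(2/180) = 0.126.
- The margin is the ratio 1.5 used in the sample size.

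Formulas:

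- Full screening against control, intact catch 7.5, full reversion: observed mean = 7.5 × (15/7.5)^f = 7.5 × 2^f; reduction = 1 − mean/15.
- Ceiling 7.5 against full screening 5.0 (at the margin): ratio = 1.5 / (15/5)^f = 1.5 / 3^f with full reversion, or 1.5 / 3^(f/2) with half reversion.
- Chance of wrongly declaring the ceiling as effective: Φ(−1.96 + f × ln 3 / SE) with full reversion; half that shift with half reversion.

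| f | Full-screening catch | Apparent reduction | Ratio, full reversion | Ratio, half reversion | Wrong declaration, full | Wrong declaration, half |
|---|---|---|---|---|---|---|
| 0 | 7.50 | 50% | 1.50 | 1.50 | 2.5% | 2.5% |
| 1% | 7.55 | 49.7% | 1.48 | 1.49 | 3.1% | 2.8% |
| 5% | 7.76 | 48.2% | 1.42 | 1.46 | 6.4% | 4.1% |
| 10% | 8.04 | 46.4% | 1.34 | 1.42 | 13.8% | 6.4% |
| 20% | 8.62 | 42.6% | 1.20 | 1.34 | 41.2% | 13.8% |

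The direction is fixed by the rule. The size depends wholly on f and on how far the catch reverts.

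**The case against.** The strongest reply is that no harm has been shown. Nothing in the document says that an eave filled with sand, rubble and cement crumbles or is re-opened within six months. Design calls it normal local practice, and the damage rule may deliberately target the new netting and moving parts. If no eaves fail, the omission changes nothing. This stands, and it means the bias can only be stated conditionally.

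Full reversion to 15 is also severe, because the houses in question still have sound netting and tight doors whereas control houses have no screening at all. That stands too, and is why low shares and half reversion are tabulated.

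The entry-route finding comes from experimental huts, and the Background itself asks for confirmation in village houses. It shows that eaves matter, but does not say how far the catch would rise in a house with screened doors and windows.

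Separate damage definitions for the two arms are intended. That explains why the criteria differ in form, but not why an installed component is left out of one of them.

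Finally, ITT comes first and its membership does not depend on damage. A reader might infer that the main result is at risk, particularly since the sample-size section allows for houses leaving the primary analysis through non-adherence. The Analysis section does not support that inference: it analyses the endpoints under ITT and then under ATP, and only the second is touched.

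**Conclusion.** The omission is real and sits in a rule that the article states explicitly, so it is not detail left to an unseen analysis plan. As worded, a full-screened house with re-opened eaves can remain in ATP, while a ceiling house that fails at the wall edge cannot.

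A reader might go further and conclude that the ATP analysis is biased against full screening and in favour of the ceiling. The document does not support that as a fact, because it gives no rate of eave failure. What can be said is that any failure would push the result in that direction. Under the assumptions above, the effect is negligible at 1% failed and material at 10% with full reversion, where the apparent reduction is 46.4% and the ratio of 1.5 shrinks to 1.34. At 20% the ratio is 1.20 with full reversion and 1.34 with half.

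The point is confined to the second analysis set and is of minor priority.

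**What to change.** In Analysis, section b, add to the full-screening definition of badly damaged a criterion for substantial re-opening of the closed eaves, scored in the same six-month durability survey. Set the threshold before outcome data are seen, and make it comparable in severity to the batten-detachment criterion in the ceiling arm. Exclusion for any gap at all would be too strict: both arms tolerate up to four holes in the netting, and zero tolerance for eaves would hold full screening to a harder standard and could tilt ATP the other way.

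The cost is one clause in the definition and one item on a survey that is already planned. A few more full-screened houses may leave the ATP set, with a small loss of precision there. ITT does not change.

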#### c) Data exclusions

Data exclusions will be tabulated for each trial arm. The following data sets will be excluded from the analysis: (1) light trap collections on nights when the light trap was not working, (2) houses destroyed or vacated by residents, (3) houses for which the occupier withdrew consent, (4) evaporimeter readings greater than 30 mm.

#### d) Primary analysis of variables

##### Entomological data

Comparisons of mean number of mosquitoes/house between intervention groups and the control group will be made using ANOVA on the log mean catch for each house. The mean will be calculated firstly as the Williams mean (geometric mean after adding 1 to all values), and in a secondary analysis, as the arithmetic mean. To allow for the 2 comparisons being made (between the control arm and each of the two interventions), P-values less than 0.025 will be considered significant and 97.5% confidence intervals will be calculated. For the comparison between the two intervention groups, we will estimate the 95% confidence interval for the ratio of the mean catch per house. If the upper limit of this interval corresponds to a difference in catch of 2.5 or less, the ceiling intervention will be considered as effective as full screening.

Estimates of entomological inoculation rate (EIR) will be generated by multiplying the mean number of mosquitoes/adult/house/night by the sporozoite rate (adjusted for area and year) and multiplying this by the number of nights during each year. The sporozoite rate, with a 95% confidence interval, will be estimated for each arm of the trial based on the number of positive and negative pools and the number of individuals per pool, and a confidence interval for the difference between trial arms will be estimated for each pairwise comparison.

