#### b) Clinical

Our aim was to have 90% power to detect a difference in mean haemoglobin of 0.5 g/dl between the two intervention arms and the control arm in November, using a significance level of 2.5% for each of the two comparisons of intervention with control. In a recent trial in The Gambia the SD was 1.7 g/dl. A difference of 0.5 g/dl is 0.3SD. The interclass correlation (ICC) for haemoglobin in another trial in Senegal varied from 0.04 to 0.08. Assuming a similar ICC in the present trial the number of children required to detect (with 90% power) a difference of 0.5 g/dl is 166 in the control arm and 332 in each intervention arm.

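### Testing each screen against control at a fixed P < 0.025 is valid, but a Holm step-down would add about 4 to 6 points of power to show both screens effective on haemoglobin, at no cost in family-wise error

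*Protocol article*

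**What the plan says.** The decision rule is in the protocol article, Analysis, section d) Primary analysis of variables, under Entomological data. The reason given is "To allow for the 2 comparisons being made (between the control arm and each of the two interventions"), and the rule is "P-values less than 0.025 will be considered significant and 97.5% confidence intervals will be calculated".

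Sample Size Rationale, section b) Clinical, plans haemoglobin on the same footing: "90% power to detect a difference in mean haemoglobin of 0.5 g/dl", "using a significance level of 2.5% for each of the two comparisons of intervention with control". The numbers given there are "166 in the control arm and 332 in each intervention arm".

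The primary analysis of clinical data compares house means of haemoglobin by ANOVA and states no threshold of its own, so 2.5% is carried over from the planning text. No step-down or Dunnett-type procedure is mentioned.

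**The concern.** The rule tests each arm at 0.025 whatever the other arm shows. Suppose one screen has P = 0.01 and the other P = 0.03. The plan reports the second as not shown to work, although the 5% family-wise error it allows would permit the claim.

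Holm's procedure controls the same 5%. If both null hypotheses are true, an error requires at least one P below 0.025, which has probability at most 2 × 0.025 = 0.05. If only one is true, testing it at 0.05 is valid. Holm rejects everything Bonferroni rejects and sometimes more, and it needs no assumption about correlation. What is at stake is power in the case the trial hopes for, in which both screens work, mainly on haemoglobin, where power is lower than for mosquito catch.

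**Working it through.** **Inputs from the article.** Haemoglobin effect 0.5 g/dl; "In a recent trial in The Gambia the SD was 1.7 g/dl"; the ICC "varied from 0.04 to 0.08"; 166/332/332 children stated as required; 1250 children as the recruitment target; 500 houses allocated 1:2:2 (100/200/200), of which 10% may be excluded; SD of log catch 1.2; planned fall in catch from 15 to 7.5.

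**Assumptions.** Two-sided tests (the article does not say for these comparisons); the same true effect in both arms; 1250/500 = 2.5 children per house; children split 250/500/500; 0 to 10% of children not sampled in November.

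**Step 1: the plan's own figure.** With control size n and 2n per intervention arm, n = (z_alpha + z_beta)² × SD² × 1.5 / difference². For two-sided 0.025 and 90% power:

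(2.241 + 1.282)² × 1.7² × 1.5 / 0.5² = 215.2, so 216 controls before any allowance for clustering.

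The article rounds the effect ("A difference of 0.5 g/dl is 0.3SD"), which lowers this only to 207. The stated 166 is not reproduced. It matches 80% power: (2.241 + 0.842)² × 1.7² × 1.5 / 0.5² = 164.8, so 165, or 166 with a t-test.

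**Step 2: the model for both rules.** The two test statistics share the control arm, so their correlation is 332/(166 + 332) = 2/3. Each has mean d = difference / [SD × √(DE × (1/n + 1/2n))], where the design effect is DE = 1 + (2.5 − 1) × ICC, that is 1.06 at ICC 0.04 and 1.12 at ICC 0.08.

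- Plan: both arms are positive with probability B = P(|Z1| > 2.241 and |Z2| > 2.241).
- Holm: both are positive if one P is below 0.025 and the other below 0.05, so H = 2 × P(|Z1| > 2.241 and |Z2| > 1.960) − B.
- The gain is H − B.

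**Step 3: results (bivariate normal).**

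| Case | d | Power per comparison, plan | Both arms, plan | Both arms, Holm | Gain (points) |
|---|---|---|---|---|---|
| Hb, 166/332/332, DE 1 | 3.094 | 80.3% | 71.2% | 79.5% | 8.3 |
| Hb, 250/500/500, DE 1.06, all sampled | 3.688 | 92.6% | 88.2% | 92.7% | 4.5 |
| Hb, 250/500/500, DE 1.12, all sampled | 3.588 | 91.1% | 86.0% | 91.1% | 5.1 |
| Hb, 250/500/500, DE 1.06, 10% not sampled | 3.499 | 89.6% | 83.8% | 89.5% | 5.7 |
| Hb, 250/500/500, DE 1.12, 10% not sampled | 3.404 | 87.8% | 81.2% | 87.5% | 6.3 |
| Hb, if power per comparison were 90% | 3.523 | 90.0% | 84.4% | 89.9% | 5.5 |
| Catch, 50% reduction, 100/200/200 houses | 4.716 | 99.3% | 98.8% | 99.4% | 0.6 |
| Catch, 50% reduction, 90/180/180 houses | 4.474 | 98.7% | 97.8% | 98.9% | 1.1 |

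For catch, d = ln 2 / [1.2 × √(1.5/n)]. A simulation of 1,000,000 trials gave 71.2% and 79.5% for the first row.

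**Step 4: where the gain comes from.** Under the global null with correlation 2/3, the fixed 0.025 rule has a family-wise error of 4.4%. Using the correlation alone (single-step Dunnett) lowers the critical value from 2.241 to 2.187, a per-comparison level of 0.0287. At 166/332/332 this raises both-arm power from 71.2% to 73.1%, or 1.9 points. Step-down Dunnett gives 79.8%, against 79.5% for Holm. Nearly all of the gain is therefore the step-down.

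**The case against.** The strongest reply is that nothing here is wrong. The rule is prespecified, is the same in planning and analysis, controls family-wise error, and has intervals that always agree with the test. Choosing simple matching intervals in a proof-of-concept trial is legitimate. All of that stands, and it makes this an efficiency point.

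Three stronger readings are tempting and are not supported.

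- A reader might take 8 points as the loss in the planned trial. That figure belongs to 166/332/332, which gives about 80% power per comparison and not the stated 90%. At the recruitment target the gain is smaller. The shortfall of 166/332 is a separate sample-size matter.
- A reader might infer a similar loss for mosquito catch, since the quoted rule sits under that heading. At the planned 50% reduction the gain is about 1 point. Larger gains need a smaller true reduction, for example about 7 points at 40% with 90/180/180 houses, but the article says at least 50% is needed for practical value.
- A reader might blame the shared control arm. Ignoring it costs only about 2 points at 166/332/332.

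The gain also depends on both screens working. If only one works, the two rules have nearly the same power to show it (80.3% under the plan against 80.4 to 81.9% under the alternatives, at 166/332/332).

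Holm also gives up the exact match between test and interval.

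**Conclusion.** This is a cheap improvement and not an error. The fixed 0.025 threshold is valid but stricter than the family-wise 5% requires once one arm has been shown effective. The expected benefit is about 4 to 6 points of both-arm power on haemoglobin at 1250 children, about 8 points if only 166/332/332 children were analysed, and about 1 point for mosquito catch.

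The haemoglobin figures rest on two-sided tests, a true 0.5 g/dl effect in both arms, and the assumed split, house size and sampling loss. They use a design-effect approximation to the planned analysis of house means. The direction does not depend on these assumptions, because Holm can never reject less than Bonferroni.

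**What to change.** In section d) Primary analysis of variables, replace the fixed threshold under Entomological data with Holm's procedure. Order the two arm-versus-control P-values and declare the smaller significant if it is below 0.025; only if it is, test the other at 0.05. State the same rule under Clinical data for haemoglobin, where no threshold is given at present. Step-down Dunnett is an optional alternative and adds little.

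Keep the 97.5% intervals. Add a note that a second arm declared effective at P between 0.025 and 0.05 may have a 97.5% interval that includes no effect.

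The cost is one sentence in each place, with no new data, houses or children. It should be settled before outcome results are seen, since a later change would look opportunistic.
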